## Discussion

Corticosteroids are considered to be the primary treatment strategy for SSNHL; however, the specific mechanism of action is unknown [14, 15]. Routes of administration include the systemic intravenous or oral route and the topical route via the round window by intratympanic injection. They are both used to increase the concentration of corticosteroids in the inner ear [8]. The therapeutic strategy of using systemic corticosteroids was based on a randomized, placebo-controlled trial performed in 67 patients that showed significantly higher rates of improvement in the corticosteroid-treated group [16]. The study demonstrated improved hearing recovery in 32% (11 of 34) of study participants in the placebo group and in 61% (20 of 33) in the steroid-treated group. Since then, this treatment strategy has been widely used. However, the effectiveness of systemic corticosteroids is still controversial [17]. A Cochrane review that was first published in 2006 and updated in 2013, found that only three trials that met their inclusion criteria with 267 study participants [18]. Two of the three trials demonstrated the lack of efficacy of systemic corticosteroids to improve hearing compared to the placebo control group. The authors concluded that the efficacy of systemic corticosteroids for the treatment of SSNHL remained uncertain. This was because the randomized controlled trials had contradictory outcomes.

Systemic corticosteroid therapy may induce potential adverse effects in several organ systems, in addition, patients may suffer from insomnia, dizziness, weight gain, increased sweating, gastritis, mood changes, photosensitivity, hyperglycemia, pancreatitis, bleeding, hypertension, cataracts, myopathy, opportunistic infections, osteoporosis, osteonecrosis manifesting as fractures, and aseptic necrosis of the femoral and humeral heads [1]. Systemic corticosteroids enhance muscle protein breakdown, adipose tissue lipolysis, and hepatic gluconeogenesis, and reduce glucose utilization, which results in hyperglycemia [19]. Corticosteroid-induced hyperglycemia requires close attention in patients with diabetes mellitus. Moreover, even short-term systemic corticosteroid administration in patients with diabetes mellitus may increase the risk of fractures, venous thromboembolism, and hospitalization for sepsis [20]. Hence, clinicians should be aware of the effects and risk of systemic corticosteroids, especially when treating patients with diabetes mellitus.

Intratympanic corticosteroid treatment is an alternative primary treatment option for patients with diabetes mellitus and SSNHL. Intratympanic administration of corticosteroids provides a direct route into the inner ear via the round window membrane, while systemic corticosteroids have a limited ability to reach the inner ear due to the blood–labyrinthine barrier [21]. Intratympanic corticosteroid administration has been shown to achieve higher concentration levels in the inner ear compared to systemic administration, in both animal and human studies [11, 22]. Several studies have shown that intratympanic corticosteroid administration is as effective as systemic corticosteroids for hearing improvement [12, 23, 24]. In 2011, Rauch et al. [12] performed a multicenter, prospective randomized controlled trial comparing the outcomes of primary treatment with oral prednisone and intratympanic methylprednisolone administration. They observed a mean PTA improvement of 30.7 dB in the oral prednisone group compared to 28.7 dB improvement in the intratympanic group. They dismissed the idea that intratympanic administration was inferior to that of oral administration.

Diabetes mellitus is a risk factor and a poor prognostic factor for SSNHL. A nationwide epidemiological survey based on 3419 patients in Japan showed that 17% of patients with SSHNL had diabetes mellitus and these patients had more severe hearing loss compared to patients who did not have diabetes mellitus [25]. In addition, several studies have shown that intratympanic corticosteroid treatment is as effective as systemic corticosteroid administration in patients with diabetes mellitus and SSHNL. Kakehata et al. [9] performed a prospective, non-randomized, comparative study of 31 patients to evaluate the efficacy of these two different types of corticosteroid administration in patients with diabetes mellitus and SSNHL. There were no significant differences between the two groups in cure rates and successful treatment. In another prospective, non-randomized clinical trial, 114 patients with diabetes mellitus and SSNHL were assigned to one of three groups: a peroral group (48 patients), an intravenous group (32 patients) and an intratympanic group (34 patients). At 8 weeks, there was a statistically significant hearing improvement before and after treatment in each group, but no significant differences were observed in hearing gain among the three groups. One patient in the peroral group and two patients in the intravenous group had uncontrolled hyperglycemia. Two patients in the intratympanic group had perforations of the tympanic membrane. However, the study quality was poor, with different corticosteroids used in the different groups. Patients with diabetes mellitus and SSNHL may benefit more when administered intratympanic corticosteroids; however, the advantage of intratympanic corticosteroids over systemic corticosteroids these patients has not been demonstrated in randomized controlled trials.

A pilot study was necessary to demonstrate the feasibility of this trial. This was performed to inform the design and was conducted from March 2018 to February 2019 in Shenzhen, China. The feasibility trail used the same prospective, randomized controlled trial to compare intratympanic corticosteroid treatment to systemic corticosteroid in patients with diabetes mellitus and SSNHL. The results demonstrated hearing improvement in the intratympanic corticosteroid group (7 patients) of 40 dB versus 30 dB in the systemic corticosteroid group. While the results supported our sample size calculation, we revised a few details in the study design for patient recruitment and trial initiation.

As a prospective, randomized, superiority trial, it is unusual that both the intratympanic and intravenous methylprednisolone group receives adjuvant therapy. We aim to conduct this trial to demonstrate both the superior efficacy and safety of intratympanic methylprednisolone over intravenous methylprednisolone for patients with diabetes mellitus and SSNHL; this trial should be able to determine which corticosteroid administration route will benefit these patients. In addition, high-quality data will be generated to determine whether intratympanic corticosteroid treatment is safe and efficacious in patients with diabetes mellitus and SSNHL.

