### Interventions

Participants in the study group will receive four 1-mL doses of 40 mg/mL of methylprednisolone over 1 week, with a dose administered every 2 days by tympanic membrane injection into the middle ear by an otolaryngologist using an operating microscope: 2% tetracaine solution will be used for local anesthesia. Patients will be in the supine position with the affected ear slightly raised and will remain in this position for 30 min after administration of the injection. Patients will also be required to avoid swallowing and vocalization during the treatment period. Patients in the control group will receive a 1-week treatment with intravenous methylprednisolone (1 mg/kg/day; the maximal dose is 60 mg/day) for 5 days, and then have 2 days off. Good Manufacturing Practice (GMP)-grade methylprednisolone will be purchased from Pfizer Manufacturing, Belgium NV.

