### Sample size calculation

The purpose of the proposed study is to compare the effectiveness of PTA by one-sided *t* test, which is used with the 95% confidence interval method. The difference in PTA is reported in previous publications as 30.7 in the experimental group and as 28.7 in the control group. The difference in the mean was 2, and the combined standard deviation was 3. The type 1 error was 2.5% and statistical power was 90%. Considering a 5% loss rate, 96 samples are required. This allows for 48 participants in the study group and 48 in the control group.

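### The 2 dB planning advantage comes from an oral-prednisone trial with the arms reversed, and the 10 dB pilot difference does not support 2 dB with SD 3

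*Protocol article*

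**What the plan says.** All references are to the protocol article.

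- **Sample size calculation.** The planning means are given as "The difference in PTA is reported in previous publications as 30.7 in the experimental group and as 28.7 in the control group". The section continues: "The difference in the mean was 2, and the combined standard deviation was 3". The test is a one-sided *t* test with type 1 error 2.5% and power 90%. With a 5% loss rate the total is 96, or 48 per arm.
- **Discussion, source trial.** The same two means appear with the opposite labels: "They observed a mean PTA improvement of 30.7 dB in the oral prednisone group compared to 28.7 dB improvement in the intratympanic group". The Background describes what appears to be the same trial (same reference number) as 250 patients with SSNHL and equivalent hearing outcomes. It does not mention diabetes.
- **Interventions.** This trial's comparator is neither oral nor prednisone: "Patients in the control group will receive a 1-week treatment with intravenous methylprednisolone". All participants have diabetes, which the Background and Discussion call a poor prognostic factor.
- **Discussion, pilot.** A feasibility trial of the same design gave 40 dB improvement with intratympanic treatment (7 patients) and 30 dB with systemic treatment. No SD, interval or control-arm number is given. The text then says: "While the results supported our sample size calculation".

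**The concern.** Two supports are offered for the sample size, and neither carries it.

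1. The published means are presented as a 2 dB advantage for the experimental arm. The article's own account of the source gives the higher figure to the systemic arm. That arm received a different drug by a different route from the control used here, in patients not described as diabetic. The source therefore offers no published 2 dB advantage for intratympanic treatment.
2. The pilot is the only dB result given for this trial's own comparison. Its difference is five times the planned one, yet it is cited as agreeing with the calculation.

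A reader would conclude that both the literature and the trial's own data back 90% power for 2 dB. In fact 2 dB and SD 3 are assumptions, and power for 2 dB falls quickly if the SD is larger than 3.

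**Working it through.** **Inputs.** Difference 2 dB, SD 3, one-sided 2.5%, power 90%, 5% loss, total 96 (Sample size calculation). Pilot 40 v 30 dB with 7 intratympanic patients (Discussion). The pilot SD and control number are not given, so values used for them below are assumptions.

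**1. The plan's own figure.** n per arm = 2 × [SD × (z₀.₉₇₅ + z₀.₉₀) / difference]² = 2 × [3 × (1.960 + 1.282) / 2]² = 47.28, rounded up to 48, total 96. This matches 96 before any loss. With 5% loss, 48 / 0.95 = 50.5, so 51 per arm and 102 in total. The 96 therefore does not contain the allowance it claims. With 5% loss, 96 randomised leave 48 × 0.95 = 45.6 evaluable per arm.

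**2. Direction of the source difference.** Intratympanic minus systemic, as labelled in the Discussion: 28.7 − 30.7 = −2.0 dB. As labelled in the sample size section: 30.7 − 28.7 = +2.0 dB. The size agrees and the sign does not.

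**3. Pilot against the pair (2 dB, SD 3).** Pilot difference = 40 − 30 = 10 dB, which is 10 / 2 = 5 times the planned value. SE = SD × √(1/7 + 1/m), where m is the unknown control number.
- m = 7, SD 3: SE = 3 × √(2/7) = 1.60. Distance from 2 dB = 8 / 1.60 = 5.0 SE. 95% CI = 10 ± 2.179 × 1.60 = 6.5 to 13.5, which excludes 2.
- m = 1, SD 3: SE = 3 × √(1/7 + 1) = 3.21. Distance = 8 / 3.21 = 2.5 SE. The misfit does not depend on the assumed 7.
- SD at which a 95% interval with m = 7 just reaches 2 dB: 8 / (2.179 × √(2/7)) = 6.9. At SD 10 the interval is −1.6 to 21.6.

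So either the difference is not 2 dB or the SD is well above 3. The pilot cannot say which.

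**4. What the sample delivers.** Power from the noncentral *t* distribution, with noncentrality = difference / (SD × √(2/n)), one-sided 2.5%, for a 2 dB difference. SDs other than 3 are assumed.

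| SD | n = 48 per arm: noncentrality, power | n = 45.6 per arm: noncentrality, power |
|---|---|---|
| 3 | 3.27, 90% | 3.18, 88% |
| 5 | 1.96, 49% | 1.91, 47% |
| 10 | 0.98, 16% | 0.95, 15% |

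The difference detectable with 90% power is about 0.67 SD at 48 evaluable per arm and about 0.69 SD at 45.6. For a 10 dB difference, 48 per arm gives 90% power up to an SD of about 15.

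**The case against.** **A larger pilot effect is good news.** A sample sized for 2 dB is not undermined by a bigger difference in the same direction, and the claim of support could mean only that 96 is enough. This has some force: at 10 dB, 48 per arm is ample for any SD up to about 15. But that is a different calculation, and it needs a pilot SD that is not reported and a 10 dB effect taken from 7 intratympanic patients. It does not support the calculation that is written down.

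**Borrowing from a related trial is normal.** It is, particularly where randomised evidence in diabetic patients is lacking, and the Discussion names oral prednisone openly. A poorer prognosis in diabetes need not change the difference between arms. This stands as a defence of using the source. It does not excuse the reversed labels, or a sample size section that does not say whose results it uses.

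**Stronger readings that the documents do not support.**
- *That the pilot disproves SD 3.* It reports no SD. Only the pair (2 dB, SD 3) fits it poorly.
- *That the SD is really about 15 and power for 2 dB about 9%.* An SD of 15 is merely the value that makes 48 per arm the 90% size for 10 dB. It appears nowhere in the article.
- *That the pilot is the only evidence on an intravenous control.* The Discussion also cites a non-randomised study in diabetic patients with 32 intravenous and 34 intratympanic patients and no significant difference in hearing gain, but without dB values. The pilot text itself says systemic; that this means intravenous is inferred from its being the same trial design.
- *That SD 3 comes from the oral-prednisone trial.* Only the means can be traced there.
- *That the true effect is −2 dB and the trial has almost no chance of success.* The source used another comparator and population, and its outcomes are described as equivalent. It does not establish an effect of −2 dB here.

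**Conclusion.** The point holds in this form. The planning means come from a different comparator, in patients not described as diabetic, and favour the systemic arm by 2 dB, so the 2 dB advantage is an assumption and not a published result. The pilot difference of 10 dB does not fit 2 dB together with SD 3: it is about 5 SE away at an assumed 7 per arm and about 2.5 SE away with a single control patient. With one small arm and no SD, the pilot confirms neither input. The statement that it supported the calculation is wrong.

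The 90% power for 2 dB depends on SD 3 and on 48 evaluable patients per arm. After the stated 5% loss it is about 88%, and it falls to about half if the SD is 5. The alternative SDs are illustrations, not estimates for this population.

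**What to change.** 1. **Discussion, pilot paragraph.** Delete the statement that the pilot supported the sample size. Report the 10 dB difference with both arm sizes and the SDs, and say that it confirms neither 2 dB nor SD 3.
2. **Sample size calculation.** Say that the source compared oral prednisone (30.7 dB) with intratympanic methylprednisolone (28.7 dB) in SSNHL patients not described as diabetic. Correct the arm labels, present 2 dB as an assumed advantage, and give the source of SD 3.
3. **Deliverable power.** State that 96 randomised with 5% loss (about 45.6 evaluable per arm) give about 88% power for 0.67 SD (2 dB at SD 3), or 90% for about 0.69 SD. Add power for 2 dB over an explicitly assumed SD range, such as 90% at SD 3, 49% at SD 5 and 16% at SD 10 with 48 per arm.
4. While editing, reconcile the 96 with the 86 patients given under Design and setting.

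The cost is wording only, with no added patients. The downside is that the stated power becomes less favourable, and the article can no longer cite a published or pilot basis for 2 dB.

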### Trial status

Protocol version 1.0; 22 September 2017. Recruitment began on 1 March 2018 and will be completed by June 2022.

## Data Availability

Not applicable.

## Abbreviations

HbA1C: Glycosylated hemoglobin
PTA: Pure-tone average
SSNHL: Sudden sensorineural hearing loss
